## Abstract

**Background:**

Adolescent mental health care is constrained not only by limited treatment capacity but also by the absence of precise and efficient tools to identify and triage those in need. Measurement-based mental health care relies on standardized assessments to guide identification, treatment selection, and ongoing monitoring of mental disorders. However, conventional assessments present a trade-off: diagnostic interviews lack feasibility at scale, while brief screening tools result in misclassification and suboptimal allocation of limited mental health resources. Computerized adaptive testing addresses this trade-off by dynamically tailoring assessments to individuals, maximizing measurement precision while minimizing assessment burden. Despite these advances, no adaptive assessment for adolescent mental health has been developed or calibrated using African data.

**Objective:**

The AfriCAT study aims to develop and internally validate a precision computerized adaptive assessment of adolescent depression and anxiety using nationally representative Kenyan data, with the longer-term goal of supporting measurement-based mental health care across diverse African contexts.

**Methods:**

AfriCAT is a mixed methods study integrating psychometric modeling, adaptive simulation, modular clinical decision support networks, participatory workshops, discrete choice experiments (DCEs), and stakeholder interviews. *Diagnostic Interview Schedule for Children, version 5* (*DISC-5*) modules assessing major depressive disorder, generalized anxiety disorder, social phobia, and posttraumatic stress disorder among adolescents aged 10 to 17 years from the Kenya National Adolescent Mental Health Survey (N=5155) will form the item bank. Adaptive engines will be developed using a bifactor multidimensional item response theory framework and a modular neural architecture. Simulation-based internal validation will evaluate precision, efficiency, and diagnostic classification relative to *DISC-5* diagnoses. Participatory workshops in Kenya and South Africa, DCEs to quantify adolescent preferences, and stakeholder interviews will inform refinement of adolescent- and provider-facing prototypes.

**Results:**

Ethical approval has been obtained from the Human Research Ethics Committee (Medical) at the University of the Witwatersrand and the Aga Khan University Institutional Scientific and Ethics Review Committee. Data preparation and model development are underway. Participatory workshops and DCEs are ongoing. Simulation-based validation and prototype refinement will follow.

**Conclusions:**

AfriCAT aims to develop the first adaptive mental health assessment calibrated using nationally representative African adolescent data. By integrating precision psychometrics with participatory co-design, the study seeks to enable more accurate triage and support scalable, measurement-based adolescent mental health care in resource-constrained settings.

## Introduction

### Background

Mental health conditions are among the leading causes of disability among adolescents globally [1]. Depression and anxiety disorders contribute substantially to the global burden of disease in young people and are associated with impaired functioning, reduced educational attainment, and increased risk of suicide [1,2]. In many low- and middle-income countries (LMICs), including those in sub-Saharan Africa, the majority of adolescents with mental health conditions do not receive appropriate care due to shortages of specialist providers, limited mental health literacy, stigma, and weak integration of mental health services within primary care systems [3].

To address these challenges, there has been growing interest in task-shared and stepped-care models of mental health service delivery, alongside the use of digital mental health interventions [4]. Task-sharing enables nonspecialist providers, including primary health care workers and trained lay counselors, to deliver evidence-based psychological interventions while reserving specialist services for more severe or complex cases [5]. Digital tools, including mobile- and web-based platforms, have also been explored as scalable approaches to delivering low-intensity mental health support [6-8]. Within stepped-care systems, these approaches can complement one another by enabling adolescents to access different levels of care based on symptom severity and clinical need [9]. However, effective implementation of such models requires efficient and scalable assessment tools to support identification, treatment planning, and monitoring of treatment response.

Measurement-based mental health care (MBMH) refers to the systematic use of standardized assessments to inform clinical decision-making across the care pathway [10,11]. Within MBMH frameworks, symptom measures are used not only to identify individuals who may require care but also to guide treatment selection and monitor symptom change over time [10-12]. Digital technologies increasingly enable such assessments to be embedded within scalable care platforms, facilitating self-monitoring and supporting clinical decision-making during consultations [9]. Although evidence from high-income settings suggests that measurement-based approaches can improve clinical outcomes, implementation in LMICs remains limited [12,13]. One reason is that commonly used assessment tools may be inefficient or poorly suited to repeated measurement in resource-constrained health systems [14].

Most widely used screening instruments, including the Patient Health Questionnaire-9 and Generalized Anxiety Disorder-7 scales, are static questionnaires that administer the same set of items to all respondents regardless of symptom severity [15,16]. Although brief and easy to administer, these instruments offer limited measurement precision across the full spectrum of symptom severity and can become burdensome when used repeatedly for treatment monitoring [17,18]. These limitations are compounded by the high degree of comorbidity between depression, anxiety, and other mental health conditions, requiring administration of multiple disorder-specific symptom scales [19]. Many existing digital mental health assessment tools similarly replicate static paper-based questionnaires, administering identical item sets irrespective of individual symptom profiles, meaning that digital delivery alone does not necessarily improve the efficiency or utility of assessments [20].

Computerized adaptive testing (CAT) offers an alternative approach to mental health assessment [20-22]. CAT uses statistical models, typically derived from item response theory, to dynamically select questions that provide the greatest informational value for each respondent [21]. As a result, adaptive tests can achieve measurement precision comparable to full-length instruments while administering substantially fewer items [21,23]. Adaptive testing approaches have been successfully applied to the assessment of depression, anxiety, and other psychiatric symptoms, demonstrating improved efficiency without compromising diagnostic accuracy [24,25]. Further, by drawing from large item banks spanning multiple symptom domains, they can estimate underlying dimensional constructs that cut across diagnostic categories and may therefore provide a more efficient means of assessing multiple mental health conditions simultaneously [21]. The adaptive item selection of CAT-based measurement also helps reduce familiarity-related responder bias, as individuals are less likely to encounter the same fixed set of items during repeated assessments.

Despite these advances, adaptive mental health assessments have largely been developed using data from high-income countries, with limited representation of adolescents from African settings. Moreover, adaptive assessments have rarely been explicitly conceptualized as tools to support measurement-based mental health care within resource-constrained health systems. Evidence is also limited regarding the feasibility, acceptability, and appropriateness of adaptive mental health assessments among adolescents in African contexts or how such tools might be integrated into existing stepped-care service models.

### Conceptual Framework

The AfriCAT study was designed to address these gaps by developing a computerized adaptive assessment for depression and anxiety among adolescents using nationally representative data from Kenya. Importantly, AfriCAT is conceptualized not as a screening tool alone but as a scalable adaptive assessment engine embedded within a stepped-care system to support measurement-based mental health care.

Within this framework (Figure 1), adaptive assessment contributes to 3 core functions across the care pathway. First, it supports identification by estimating the probability of depressive and anxiety disorders and generating dimensional severity scores. Second, these outputs inform triage, enabling stratification of individuals into levels of care based on symptom severity and risk, ranging from low-intensity, high-volume interventions to more intensive, clinician-supported services. Third, repeated adaptive assessments enable measurement-based care, allowing providers to monitor symptom trajectories and adjust treatment through step-up or step-down transitions over time.

**Figure 1. F1:**
[figure not shown]
Adaptive assessment within a stepped-care, measurement-based mental health care framework.

Importantly, the framework incorporates risk-responsive pathways, whereby elevated risk (eg, suicidality) triggers immediate escalation to higher levels of care. In this way, adaptive testing functions as a continuous decision-support mechanism, informing both initial triage and ongoing management within resource-constrained, task-shared systems.

This figure illustrates how adaptive assessment supports measurement-based care through identification, triage, and ongoing monitoring within a stepped-care system. Individuals are stratified into levels of care based on symptom severity and risk, with low-intensity, high-volume interventions at the base and higher-intensity, clinician-supported care at the apex. Repeated assessment enables dynamic step-up and step-down transitions over time. Risk flags (eg, suicidality) trigger immediate escalation pathways.

### Study Aim and Objectives

The overall aim of the AfriCAT study is to develop and internally validate a computerized adaptive assessment for adolescent depression and anxiety designed to support measurement-based mental health care in African contexts. Specific objectives are as follows:

to develop and calibrate adaptive assessment models for depression and anxiety using nationally representative adolescent mental health survey data.to evaluate the precision, efficiency, and diagnostic classification performance of the adaptive assessment through simulation-based internal validation.to compare adaptive algorithms derived from multidimensional item response theory (MIRT) and modular clinical decision support network (MODN) architectures.to incorporate adolescent perspectives through participatory workshops and discrete choice experiments (DCEs) to inform tool design and implementation.to assess stakeholder perspectives regarding the feasibility and potential integration of adaptive assessment into existing mental health systems.

## Methods

### Study Design

AfriCAT is designed as a multicomponent mixed methods study that integrates psychometric modeling, adaptive algorithm development, and participatory co-design.

The first component involves secondary analysis of nationally representative survey data to calibrate and simulate adaptive assessment models. In parallel, 2 complementary adaptive approaches will be developed: a MIRT-based framework grounded in latent trait estimation [26], and a MODN architecture designed to support sequential, consultation-aligned diagnostic updating [27].

Building on these adaptive engines, digital prototypes will be developed for both adolescent self-administration and provider use within primary care settings using task-sharing. The development process will be informed by participatory workshops with adolescents who have lived experience of depression and anxiety, as well as DCEs designed to quantify user preferences regarding key design and implementation features. In addition, semistructured interviews with mental health providers, primary health care workers, and policymakers will explore feasibility, workflow integration, and system-level considerations for scale-up. Reporting will align with established guidance on predictive modeling, participatory engagement, and mixed methods integration [28-30].

This study does not constitute a clinical trial. The present protocol focuses on tool development and internal validation within existing data. External validation in independent samples, including prospective clinical validation studies in Kenya and South Africa, will be undertaken in subsequent research before broader implementation is considered (Figure 2).

**Figure 2. F2:**
[figure not shown]
Logic model for the AfriCAT study. CAT: computerized adaptive testing; DCE: discrete choice experiment; MBMH: measurement-based mental health care; MIRT: multidimensional item response theory; MODN: modular clinical decision support network.

AfriCAT consists of three workstreams: (1) CAT modeling using MIRT and MODN; (2) engagement with adolescents with lived experience through participatory workshops and DCEs; and (3) engagement with mental health providers and policymakers through in-depth interviews. Outputs will be integrated into the AfriCAT prototypes. Further research will address the intended outcomes and impact.

### Lived Experience

Incorporating adolescents’ lived experiences of depression and anxiety is essential to ensure the tool reflects how young people experience and articulate their symptoms [31]. In this study, lived experience is defined as personally identifying as having experienced depression and/or anxiety; a formal clinical diagnosis is not required. Lived experience is embedded within AfriCAT at multiple levels. Youth Liaisons in Kenya and South Africa with lived experience are incorporated into the study team as coresearchers, contributing to study design, refinement of research materials, data collection, interpretation of findings, and dissemination. In addition, adolescents with lived experience are engaged in a series of participatory workshops and DCEs in Kenya and South Africa. Together, these approaches ensure that youth perspectives shape tool development, strengthening the acceptability and contextual relevance of the adaptive assessment.

### Study Settings

Participatory workshops and DCEs will be conducted in Nairobi, Kenya, and in 2 settings in South Africa: Agincourt (Mpumalanga Province) and Johannesburg. These sites reflect diverse urban and rural contexts within sub-Saharan Africa where adolescent mental health needs are substantial and service capacity remains constrained [32-34]. Mental health literacy among adolescents and caregivers varies considerably, and stigma continues to influence help-seeking behavior across both countries [35,36]. At the same time, both Kenya and South Africa have experienced rapid expansion in mobile phone access and digital connectivity among young people, creating opportunities for scalable digital mental health interventions [37,38]. Kenya has been recognized as a regional leader in mobile health innovation, while South Africa has articulated national digital health strategies that support integration of digital tools within primary care systems [39,40]. These contextual factors make Nairobi, Agincourt, and Johannesburg particularly relevant settings for examining the acceptability, feasibility, and implementation potential of a computerized adaptive assessment designed to advance measurement-based adolescent mental health care in resource-constrained systems.

### Item Bank Development

The AfriCAT item bank will be constructed from symptom-level items within the *DISC-5* modules assessing MDD, GAD, SoPh, and PTSD. These conditions represent the most common internalizing mental health conditions in adolescence and are characterized by substantial symptom overlap and comorbidity, making them well suited to dimensional measurement approaches [19]. These modules were also administered directly to adolescents (as opposed to caregivers), reducing complexity for purposes of developing an adaptive assessment [42]. Externalizing modules (eg, attention-deficit/hyperactivity disorder and conduct disorder) were excluded to maintain a coherent internalizing measurement framework.

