### MIRT-Based CAT Development

To capture the latent structure of symptoms appropriately, a bifactor multidimensional framework is outright adopted for model calibration. Within this definitive framework, all items load directly onto a single general internalizing factor while simultaneously contributing to independent, disorder-specific factors corresponding to MDD, GAD, SoPh, and PTSD. Model fit for this bifactor configuration will be rigorously assessed by evaluating the strength and significance of item factor loadings, examining global fit statistics, specifically the limited-information M2 statistic alongside absolute and relative indices such as the root mean square error of approximation and the comparative fit index, and visually inspecting observed versus expected item response plots to identify localized areas of measurement.

*DISC-5* symptom items in the K-NAMHS dataset are recorded as binary (yes/no) responses, indicating the presence or absence of specific symptoms. Item parameters will therefore be estimated using dichotomous item response theory models, allowing estimation of item discrimination and severity parameters for each symptom indicator. The baseline MIRT bifactor calibration will be executed via a stochastic expectation-maximization algorithm. To ensure population representativeness, normalized complex survey weights will be integrated directly into the estimation process to scale individual contributions to the marginal likelihood. Missing data handling strategies will differ by analytical phase. For the core MIRT calibration, missingness will be accommodated via full-information maximum likelihood, which leverages all available structural information without data loss. However, because post hoc adaptive testing simulations within the MIRT-CAT framework require a complete matrix to execute through high-missingness skip patterns, model-based plausible value imputation will be utilized strictly to construct the complete simulation response bank.

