Adaptive simulations will iteratively select items that maximize information at the current trait estimate and allow us to determine the extent to which the CAT reproduces information in the full item bank. Item administration within the CAT engine will cease when the SE of the general factor theta estimate falls below a specified precision threshold, which is optimized to maximize the posttest correlation coefficient with full-bank estimates. Alternatively, administration will stop when a maximum question cap is reached to minimize respondent burden, allowing us to balance measurement precision with assessment length.

Model performance and operational efficiency will be evaluated through post hoc adaptive simulations executed across the entire calibrated dataset, adhering strictly to established psychometric validation standards for multidimensional screening tools.

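### The bifactor model has no term, and the plan no pairwise check, for same-symptom items in different modules, so the general-factor SE that stops the adaptive test may be too small

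*Protocol article*

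**What the plan says.** Under Item Bank Development, "The AfriCAT item bank will be constructed from symptom-level items within the" DISC-5 modules for MDD, GAD, SoPh and PTSD. The section justifies pooling them by saying the conditions are "characterized by substantial symptom overlap and comorbidity". It lists no items or item count, and mentions no merging of repeated symptoms.

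Under MIRT-Based CAT Development, the structure is fixed in advance: "a bifactor multidimensional framework is outright adopted for model calibration". In it, "all items load directly onto a single general internalizing factor while simultaneously contributing to independent, disorder-specific factors", one per disorder. Fit is judged by the loadings, by "examining global fit statistics, specifically the limited-information M2 statistic" with RMSEA and CFI, and by "visually inspecting observed versus expected item response plots to identify localized areas of measurement".

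The same section selects each next item by maximum information. Administration will "cease when the SE of the general factor theta estimate falls below a specified precision threshold", or end at a question cap. The SE threshold is tuned to give the highest correlation with full-bank scores, and items missing through skip patterns are filled by imputation from the model. Neither the threshold nor the cap is given as a number.

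**The concern.** The overlap that motivates pooling the modules has no place in the model. If a symptom relevant to two conditions is asked in two modules, the answers will tend to agree beyond what general severity explains, because they concern the same symptom. The model has no parameter for that agreement. It is partly absorbed into the general loadings, and the second answer is counted as fresh information about the general trait.

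Two things are at stake. The SE that decides when to stop may be too optimistic, so any precision figure reported from it would be overstated. Unconstrained selection can also spend questions on a symptom already asked, and the median number of items is a primary metric under Primary Outcomes.

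The later steps would not readily expose this. The tuning benchmark is the full-bank score from the same model. Imputed answers are generated from the fitted model, and so follow its independence assumption.

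**Working it through.** The article gives no precision figure to reproduce, so the check is of the mechanism and its plausible range.

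**1. What the model implies.** Write the latent response to item j as g_j·G + s_j·S(module) + residual. For items j and k in different modules, the model allows a correlation of g_j·g_k only. If both also load c on a shared symptom term, the true correlation is g_j·g_k + c_j·c_k. With an assumed general loading of 0.625:

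- model form: 0.625² = 0.391
- with c = 0.3: 0.391 + 0.09 = 0.481
- with c = 0.5: 0.391 + 0.25 = 0.641

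The gap either inflates the general loadings or stays as unmodelled dependence. Both make the general-factor SE too small.

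**2. Simulation (probit).** Every setting is an assumption: 48 binary items in 4 modules, general loadings 0.50-0.75, specific loadings 0.25-0.50, mean threshold 1.0, SE stop 0.40, cap 20. Each same-symptom cluster spans 3 modules, and its items have similar loadings and thresholds. The plan's bifactor form was fitted without the clusters. Maximum-information testing with EAP scoring was then run on 3 × 2,500 respondents per row. SE, RMSE and their ratio are for tests that stopped on the SE; the other columns cover all respondents.

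| Clusters | c | Items | Repeats | Stopped on SE | SE | RMSE | RMSE/SE | r with full bank |
|---|---|---|---|---|---|---|---|---|
| 0 | 0 | 18.3 | 0 | 39% | 0.396 | 0.395 | 0.998 | 0.976 |
| 3 | 0.3 | 17.8 | 2.4 | 42% | 0.395 | 0.402 | 1.018 | 0.974 |
| 3 | 0.5 | 17.6 | 2.4 | 44% | 0.395 | 0.421 | 1.064 | 0.973 |
| 5 | 0.3 | 17.7 | 3.5 | 43% | 0.395 | 0.400 | 1.013 | 0.975 |
| 5 | 0.5 | 17.5 | 3.6 | 45% | 0.395 | 0.433 | 1.095 | 0.973 |
| 5 | 0.6 | 17.7 | 3.7 | 45% | 0.396 | 0.441 | 1.115 | 0.971 |
| 8 | 0.5 | 17.6 | 5.2 | 46% | 0.395 | 0.428 | 1.083 | 0.970 |

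- *Simulation error.* About 0.427 × 7,500 ≈ 3,200 tests stopped on the SE, so the ratio has a standard error near 1/√(2 × 3,200) ≈ 0.0125. The two rows with c = 0.3 cannot be told from 1.00. The others can.
- *All respondents, including those at the cap.* RMSE/SE is 0.469/0.472 = 0.99 without overlap. With overlap it runs from 0.469/0.466 = 1.01 to 0.507/0.465 = 1.09.
- *Repeats.* From 2.4/17.8 ≈ 13% to 5.2/17.6 ≈ 30% of questions concerned a symptom already asked.
- *Visibility.* The correlation with full-bank scores moved only from 0.976 to 0.970-0.975. The root mean square residual correlation was 0.008-0.038.

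**3. Second simulation (logistic, EM calibration at N = 5,155).** It also assumed 48 items, SE stop 0.40 and cap 20, with 12 or 24 items repeating 4 or 8 symptoms across 3 modules. Same-symptom residual correlations were 0.23-0.55. Among tests stopped on the SE, error variance exceeded nominal by 7-18% (12 items) or 10-23% (24 items), against 1-2% without dependence. On the SE scale, √1.07 = 1.03 and √1.23 = 1.11, so the excess is about 3-11%, in line with step 2. Allowing one item per symptom cut the variance excess to 3-5% at 0.5-1.4 more items. Correlation with the true trait was 0.896 against 0.889-0.896 (12 items), and 0.892 against 0.882-0.891 (24 items).

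**The case against.** The strongest objection is that the article describes overlap between conditions, not duplicate items. A reader might infer that the test will repeat symptoms and that its SE is wrong. The documents do not support that: they list no items and give no residual correlations, and both simulations put the duplicates in by assumption. This stands, and it makes the point conditional.

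A reader might also infer that tests will stop markedly early. That is not supported either. Mean length fell by only 0.5-0.8 items, and 54-58% of respondents in the overlap rows ended at the cap. The threshold is also tuned, not fixed, so it may shrink along with the nominal SE. The tuning does not correct the SE, however, because its benchmark shares the model.

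Nor does the article define its precision metric as the model SE. The claim that repeats waste questions is not shown, since no comparison at equal test length was made.

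M2 uses bivariate margins and could respond to such misfit. No M2, RMSEA or CFI was computed here, so it is not established that these indices would look acceptable. What remains is that a global index does not name the pair responsible, and a plot of one item against its expected response is not a pairwise check.

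Finally, a condensed article may leave dependence screening to a fuller plan. That is possible. But this section sets out its model, fit checks, selection and stopping rules, and none of them covers the point.

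**Conclusion.** The point holds in conditional form. Independence across modules given the general factor follows directly from the stated model, and positive residual dependence between same-symptom items makes the general-factor SE too small. Under the assumed overlap, the understatement runs from negligible to moderate: about 1-12% on the SE scale, with the lower end within simulation error. That range rests on assumed bank size, loadings, overlap, SE stop and cap; the real figure is unknown. An optimistic SE is the firmer consequence, and shortened tests a minor one. This is a worthwhile, inexpensive improvement and does not invalidate the bifactor approach. The Results section says calibration is underway and simulation will follow, so it can still be made.

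**What to change.** 1. In Item Bank Development, map the items that ask the same symptom in more than one module.
2. In MIRT-Based CAT Development, after calibration, add a pairwise residual-dependence check (for example the Q3 residual-correlation statistic). Run it on observed responses, not on the imputed simulation bank.
3. For flagged cross-module sets, either add a shared residual term or count only one item per set toward the general-factor SE. Keep the other items available for disorder-specific scoring and classification, which Primary and Secondary Outcomes require. Simply deleting them could cost that content.
4. Restrict selection so that flagged duplicates are not both given for the general-factor estimate.
5. Report the SE and the median number of items with and without this handling.

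The cost is some analysis wording, one extra diagnostic run, and perhaps about one more question per test to reach the same nominal SE (0.5-1.4 in the second simulation). The effect on disorder-specific classification was not simulated, so the with-and-without report should cover it too.
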